#### **4.3.2 Exclusion criteria**

Patients who meet any of the following criteria will not be accepted:

- patients to whom the use of anticoagulants is contraindicated (patients using other anticoagulants, or with active bleeding, or with hypersensitivity to warfarin, or with ulcers);
- women of childbearing age, or who are pregnant or breastfeeding;
- patients with thrombocytopenia;
- patients with liver or kidney failure;
- patients with a history of bleeding episodes due to congenital deficiency of coagulation factors;
- patients enrolled in other clinical trials;
- patients not reaching a TTR of at least 70% in the first phase of the study (will be considered non-adherent to therapy);
- patients starting treatment with drugs that are contraindicated or that incur in moderate or major interactions when used concomitantly with warfarin, according to the online database Micromedex 2.0 (37) (Annex II).

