##### **4.6.2 Statistical analysis**

All statistical analyzes will have a significance level of 5%. Paired-samples t-tests (also called dependent T-tests) will be used for the outcome of mean INR and PT. Analysis will be performed by protocol for these outcomes i.e., data from patients who start treatment with any drugs that interact with warfarin as previously defined (list in Annex II) will be excluded from the final analysis.

The dichotomous outcomes (TTR, thromboembolic events, bleeding) will be analyzed by McNemar's test. Exploratory analyzes for patient subgroups are not planned. The dichotomous variables will be analyzed by intention to treat, considering the missing data as an unfavorable outcome, in which case a sensitivity analysis will be carried out to assess the robustness of the result.

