### Major

|                        |                        |                         |                   |                             |               |
|------------------------|------------------------|-------------------------|-------------------|-----------------------------|---------------|
| abciximab              | cephalothin sodium     | enzalutamide            | leflunomide       | Papaya                      | teriflunomide |
| acenocumarol           | cephapirin             | eptifibatide            | lepirudin         | paroxetine                  | testosterone  |
| alefacept              | cephradine             | erlotinib               | levofloxacin      | penicillin G                | ticarcillin   |
| amiodarone             | Chamomile              | erythromycin acistrate  | lomitapide        | penicillin V benzathine     | ticlopidine   |
| amoxicillin            | ciprofloxacin          | escitalopram            | Lycium            | pentosan polysulfate sodium | tinzaparin    |
| ampicillin trihydrate  | citalopram             | etoposide               | Marijuana         | phenindione                 | tirofiban     |
| apixaban               | clarithromycin         | etravirine              | mechlorethamine   | phenprocoumon               | torsemide     |
| aprepitant             | clopidogrel            | fenofibrate             | methicillin       | piperacillin                | valproic acid |
| aspirin                | cloxacillin benzathine | fenofibric acid         | methotrexate      | Pomegranate                 | venlafaxine   |
| azythromycin           | Cranberry juice        | fibrinolytic agents     | Methyl salicylate | posaconazole                | vilazodone    |
| bivalirudin            | cyclophosphamide       | Fish oil                | metronidazole     | prasugrel                   | vincristine   |
| capecitabine           | dabigatran             | fluconazole             | miconazole        | procarbazine                | vindesine     |
| carbenicillin disodium | dabrafenib             | fluoruracil             | milnacipran       | proguanil                   | voriconazole  |
| carboplatin            | dalteparin             | fluoxetine              | moxalactam        | rivaroxaban                 |               |
| cefadroxil             | danaparoid             | fluvoxamine             | moxifloxacin      | ropinirole                  |               |

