## Moderate

|                    |                       |                               |                      |                         |                          |
|--------------------|-----------------------|-------------------------------|----------------------|-------------------------|--------------------------|
| Avocado            | benzbromarone         | ceftriaxone                   | desipramine          | exenatide               | Green tea                |
| acarbose           | betamethasona         | Celery                        | Devil's claw         | ezetimibe               | griseofulvin             |
| acemetacin         | bicalutamide          | Chaparral                     | dexamethasone        | felbamate               | Guggul                   |
| acetaminophen      | Bilberry              | chitosan                      | dexlansoprazole      | fenbufen                | halothane                |
| Agrimony           | bismuth subsalicylate | chloral hydrate               | dexmethylphenidate   | fenoprofen              | heparin calcium          |
| alclofenac         | Black cohosh extract  | chloramphenicol               | dextropropoxifeno    | Fenugreek               | heptabarbital            |
| Alfalfa            | Black currant         | chlordiazepoxide              | diazoxide            | Feverfew                | hexobarbital sodium      |
| allopurinol        | Black haw             | chlorotrianisene              | diclofenac           | floctafenine            | High protein food        |
| Aloe               | Black tea             | chlormpromazine hydrochloride | diethylstilbestrol   | flosequinan             | Horse chestnut           |
| aminoglutethimide  | Bladderwrack          | cholestyramine                | diflunisal           | fludrocortisone acetate | Horseradish              |
| amitriptyline      | boceprevir            | chondroitin                   | dipyrone             | flufenamic acid         | hydrocortisone           |
| amobarbital sodium | Bogbean               | cimetidine                    | disopyramide         | fluoxymesterone         | ibritumomab              |
| amoxapine          | Boldo                 | Cinchona                      | disulfiram           | flurbiprofen            | ibuprofen                |
| amprenavir         | Borage                | cisapride monohydrate         | Dong quai            | flutamide               | ifosfamide               |

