|                            |                             |                      |                  |                           |
|----------------------------|-----------------------------|----------------------|------------------|---------------------------|
| lornoxicam                 | Noni juice                  | propiltiouracil      | secobarbital     | Tonka                     |
| lovastatin                 | Nortriptyline hydrochloride | propoxyphene         | Senega           | toremifene citrate        |
| Meadowsweet                | omega-3-acid ethyl esters   | propranolol          | Skullcap         | tramadol                  |
| meclofenamate              | omeprazole                  | propyphenazone       | sorafenib        | trastuzumab               |
| mefenamic acid             | Onion oil                   | proquazone           | Soybean          | treprostinil              |
| melatonin                  | orlistat                    | protriptyline        | spironolactone   | triamcinilone acetone     |
| meloxicam                  | oxaprozin                   | Pumpkin seed         | stanozolol       | trimipramine              |
| menthol                    | oxiphenbutazone             | Quassia              | sucrafate        | valdecocix                |
| mephobarbital              | oxymetholone                | quetiapine           | sulfasalazine    | vancomycin                |
| mercaptapurine             | oxytetracycline             | quinestrol           | sulfinpyrazone   | vemurafenib               |
| mesalamine                 | pantoprazole                | quinidine            | sulindac         | vitamin A                 |
| Mesna                      | paramethasone               | quinine              | sulofenur        | vitamin E                 |
| methandrostenolone         | Parsley                     | rabeprazole sodium   | suprofen         | vitamin K (phytonadione)  |
| methylphenidate            | Passion flower              | raloxifene           | Sweet woodruff   | Vitamin K containing food |
| methylprednisolone acetate | Pau d'arco                  | ranitidine           | Tamarindo        | vorinostat                |
| methyltestosterone         | pentoxifylline              | Red clover           | teduglutide      | Wild lettuce              |
| mifepristone               | phenobarbital               | rifabutin            | telaprevir       | Willow                    |

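### The only stated analysis of mean INR excludes patients who start an Annex II drug, with no exemption when that drug was started because of the INR, a bleed or a clot

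*Protocol*

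**What the plan says.** Section 4.6.2 assigns paired t-tests to mean INR and mean PT and then fixes the analysis set: "Analysis will be performed by protocol for these outcomes". It explains at once what this means for the final analysis: "data from patients who start treatment with any drugs that interact with warfarin as previously defined (list in Annex II) will be excluded".

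The drugs meant are defined in section 4.3.2, which lists among its exclusions "patients starting treatment with drugs that are contraindicated or that incur in moderate or major interactions when used concomitantly with warfarin". The moderate list of Annex II contains "heparin calcium" and the entry beginning "vitamin K (phytonadione". The major list contains enoxaparin, dalteparin and "fibrinolytic agents".

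The other outcomes are handled differently in the same section: "The dichotomous variables will be analyzed by intention to treat, considering the missing data as an unfavorable outcome", with a sensitivity analysis. TTR, thromboembolic events and bleeding are the outcomes so treated. No analysis of INR in all randomised patients is stated.

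**The concern.** The hypothesis in section 3 is equivalence of mean INR within 0.49. In such a trial, an exclusion that removes patients with large differences between products favours the conclusion sought.

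Starting a listed drug is an event after randomisation. For most of Annex II there is no evident link with the trial outcome. For a few entries there can be one: vitamin K may be started because the INR is too high, and a heparin or a fibrinolytic because of a clot. If a patient overshoots on one product and is treated with a listed agent, the rule takes that patient's INRs out of the primary comparison. The INR that showed the problem goes with them. Whether a patient is excluded can then depend on which formulation was being taken, and randomisation no longer protects the comparison.

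**Working it through.** **1. What the rule covers.** Section 4.6.2 refers back to an earlier definition, and section 4.3.2 supplies it: contraindicated, major or moderate. Vitamin K and heparin calcium are moderate; enoxaparin, dalteparin and fibrinolytic agents are major. All are caught. Neither section makes an exception by reason for starting the drug, and neither limits the exclusion to later measurements.

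**2. The same INRs treated in two ways.** Section 4.5.2 builds TTR from time between INR 2.0 and 3.0, so TTR and mean INR come from the same measurements. Under section 4.6.2, a patient given a listed drug after a bleed stays in for TTR and for the bleeding outcome, and leaves for mean INR.

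**3. The plan's own sample size.** Inputs from section 4.6.1: difference 0.49, SD 0.29, two-sided α = 5%, power 90%.

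n per group = 2 × [0.29 × (1.960 + 1.282) / 0.49]² = 7.36, rounded up to 8; 8 × 6 = 48. Then 48 / (1 − 0.20) = 60. Both stated figures reproduce. The reserve of 60 − 48 = 12 patients replaces lost precision. It does nothing about selection.

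**4. Direction and possible size.** The protocol gives no frequency and no trigger, so this step is illustration on assumed inputs. Only the mean of 2.45 and the SD of 0.29 come from section 4.6.1, and using 0.29 as the between-patient SD is itself an assumption.

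- Patient level M ~ Normal(2.45, 0.29).
- Brand phase mean = M + e₁; generic phase mean = M + d + e₂; e₁ and e₂ have within-patient SD s.
- A patient is dropped with probability p if either phase mean exceeds a cut-off c.
- At least 1,000,000 simulated patients per scenario.

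Mean difference among retained patients when the true d is 0.49 (percentage dropped in brackets):

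| s | c = 3.0, p = 0.5 | c = 3.0, p = 1 | c = 3.5, p = 0.5 | c = 3.5, p = 1 | c = 4.0, p = 1 |
|---|---|---|---|---|---|
| 0.20 | 0.46 (22%) | 0.42 (44%) | 0.48 (3%) | 0.48 (6%) | 0.49 (0.1%) |
| 0.29 | 0.45 (23%) | 0.37 (46%) | 0.47 (4%) | 0.46 (9%) | 0.49 (0.5%) |
| 0.40 | 0.43 (25%) | 0.32 (49%) | 0.46 (7%) | 0.42 (14%) | 0.48 (1.7%) |

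With all patients kept, the expected estimate equals d. When d = 0, the retained difference is also 0: the rule hides a difference that exists and does not create one. When d = 0.60, outside the limit, the retained difference at cut-offs 3.0 and 3.5 was 0.38 to 0.59. It fell below 0.49 only when every patient above 3.0 was dropped and s was 0.29 or 0.40. In every scenario with a real difference the shift was toward zero.

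**The case against.** **Such cases may be rare, and the bias small.** This largely stands. No section says that vitamin K is given for a high INR. The response described in section 4.4.2 to an out-of-range INR is dose adjustment, and section 4.3.2 already removes patients with TTR below 70% in phase one. The left-hand columns of the table, with up to half the patients dropped, are extreme. With a cut-off of 4.0 the effect is 0.01 or less. What remains is that the direction is known and adverse, and that the stated rule contains nothing to prevent the bias.

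**Per-protocol analysis is a recognised choice for equivalence.** True, and the set need not be abandoned. But its usual justification is that it does not dilute a difference. A per-protocol set whose exclusions can follow from the outcome does not have that property, and here it stands alone.

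**The SAP may add an all-randomised analysis.** It may. The fault, though, is not an omission: the protocol states which data are excluded from the final analysis of the primary outcome.

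**The outcome-driven cases are still reported.** They are, in bleeding, thromboembolism and TTR. They are not in mean INR, on which the equivalence claim rests.

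**Three stronger readings are tempting and not supported.**

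- A reader might infer that the long list, with its common analgesics and foods, will exhaust the 12 spare patients and leave the trial underpowered. The protocol gives no rate of starting such items. The 48 also comes from a between-group formula, while the analysis is paired. With SD 0.29 per product and zero within-patient correlation (assumed), the SD of differences is 0.29 × √2 = 0.41, and even 28 pairs give over 99% power for 0.49. With an SD of differences of 0.60 the power is still about 98%.
- A reader might count aspirin, clopidogrel and omeprazole as outcome-driven too. They are listed, but nothing in the protocol links starting them to INR, bleeding or thrombosis.
- A reader might state as fact that all phases of an affected patient are deleted. That is the natural reading of the sentence, but it is not explicit.

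**Conclusion.** The point holds as a fault in the stated primary analysis set. The exclusion is post-randomisation, it can depend on the outcome and on the formulation, and no exemption or time limit is stated. The effect is toward equivalence. Its size cannot be derived from the protocol. On assumed triggers a true 0.49 shows as 0.32 to 0.49, and the milder end is at least as plausible as the severe one.

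The conclusion rests on one premise from general clinical knowledge: that vitamin K, heparins and fibrinolytics can be started because of a high INR, a bleed or a clot. It does not depend on whole-patient deletion. If only the affected phase were removed, that would still take out the INR that led to treatment, and with it that patient's pairs involving that product. Loss of sample size is not part of the case.

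**What to change.** Amend section 4.6.2 in two places.

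1. **Per-protocol set.** Keep all INRs (and PTs) measured up to the start of the interacting drug, including any value that led to it. Set aside only later values.
2. **All-randomised set.** Run the same paired comparison on all randomised patients with every INR collected. Report it beside the per-protocol result, and claim equivalence only if both support it.

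**Cost.** The start date and the reason for starting must be recorded for each listed drug, and the all-randomised set will carry some interaction noise.

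There are two limits to note. A patient who starts a listed drug in phase two has no second formulation before that date, and so forms no pair in the per-protocol set; the all-randomised set is what covers such a patient. Also, section 4.3.2 lists starting these drugs among its exclusion criteria without saying whether INR collection then stops. Sections 4.3.2 and 4.6.2 should be reconciled on this, because an all-randomised analysis can use only the INRs that are collected. No change to clinical management is proposed.

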## **1. Background**

### **1.1 Generic drugs**

In this introduction, we started describing that generic drugs represent a significant share of the drug market in Brazil and are completely incorporated in the country's health policies (1-4). We mentioned, however, that when it comes to the group of narrow therapeutic index drugs, which includes warfarin, even healthcare providers are suspicious of the equivalency of generic drugs to their branded counterparts (5-7,17-18). Next, we explained the technical requirement that generic drugs must fulfill in order to be considered equivalent to the brand medication, mentioning that some countries, but not Brazil, apply additional requirements to narrow therapeutic index drugs (7-12). Afterwards, we presented some studies that compared the effects of generic and branded warfarins. Randomized clinical trials did not show clinically meaningful differences between generic and branded warfarins, whereas observational studies brought more conflicting results. Nevertheless, none of these studies have used the generic and branded warfarins available in Brazil, limiting their applicability in our country (6, 13-16,19-21). Subsequently, we mentioned an issue that might arise when there is more than one generic drug available for a given brand medication: generics are devised to be equivalent to the brand medication, but not necessarily equivalent to each other (22). Finally, we presented the objectives of this project: run a randomized crossover clinical trial to assess whether the substitution of 1) branded warfarin by any of the generic formulations available in Brazil, or 2) substitution within the generic warfarins, is effective and safe for the patient with atrial fibrillation (AFib). We also added that patients with AFib diagnosis were selected because this was the most common diagnosis among the patients of anticoagulation clinics (23).

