## **2. Objectives**

### **2.1 Overall objective**

Determine, through the mean international normalized ratio (INR) of patients, whether there is therapeutic equivalence between brand and generic warfarin sodium tablets in patients with atrial fibrillation in Brazil.

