### **2.2 Specific objectives**

Assess the effects of the different warfarin tablets on:

- the mean INR of patients;
- the mean prothrombin time (PT);
- the proportion of thromboembolic events;
- the proportion of bleedings;
- the time in therapeutic range (TTR);
- adherence to treatment.

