### 3. Hypothesis

The comparison of the mean INR between branded and generic warfarins is within the limit of 0.49 (two-sided, with a significance level of 5%) demonstrating therapeutic equivalence between them.

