#### **4.4 Procedures**

Patients will be randomly allocated to one of the treatment sequences (A, B, C, D, E or F, Figure 1) and will start treatment with either the branded warfarin sodium or with one of the two generic versions available in the Brazilian market in August 2013. The first phase of the study will last 21 days. During this period, the patient, who had already been using warfarin, will start the randomly allocated treatment that will also be used in the second phase of the clinical trial. The use of the same treatment in phases one and two aims to avoid the carry-over effect without the interruption of anticoagulation treatment, which would be ethically unacceptable. The duration of three weeks for this phase is equivalent to about seven warfarin half-lives (38), the washout time for elimination of this drug. The duration of this phase will allow us to ensure that the formulation of warfarin used previously does not interfere with the results of the trial.

The second, third and fourth phases of the study will last 28 days each, in order to allow more weekly measurements to assess the effect of therapy with each of the formulations. In the second phase the patients will continue with the treatment started in phase one, and in the third and fourth phases will occur the change of warfarins according to the predetermined sequences for each group.

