##### **4.5.2 Secondary outcomes**

- Mean PT

The mean PT will be evaluated in the same way as the INR.

- Time within the therapeutic range (TTR).

This ratio is calculated for each patient by the percentage of person-time within the therapeutic range of 2.0 and 3.0 divided by the total person-time contribution by that same individual (39).

- Frequency of thromboembolic events

It includes ischemic stroke (differentiated from hemorrhagic stroke by tomography) and thromboembolism on the viscera or extremities (diagnosed by acute symptoms and relevant diagnostic tests) (40).

- Frequency of bleedings

Bleeding events will be classified as major or minor bleedings:

- Major bleeding: intracranial bleeding, fatal bleeding, blood loss resulting in a decrease greater than or equal to 2.0 g / L of serum hemoglobin, bleeding requiring transfusion, bleeding in sensitive areas such as the retina or pericardium.
- Minor bleeding: all other bleeding (33).

- Adherence to treatment

Adherence will be calculated by the amount of tablets returned by the patient.

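### For thromboembolic events, and for major bleeding if it is about as rare, the planned McNemar test at 5% is uninformative and should give way to descriptive reporting

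*Protocol*

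**What the plan says.** Section 1.1 (Generic drugs) describes the aim as assessing whether substitution "is effective and safe for the patient with atrial fibrillation (AFib"). Section 2.2 (Specific objectives) lists the effect of the tablets on "the proportion of thromboembolic events" and on bleedings. Section 4.5.2 (Secondary outcomes) divides bleeding into two grades. The severe grade begins "Major bleeding: intracranial bleeding, fatal bleeding" and also includes a haemoglobin fall of 2.0 g/L or more. All remaining bleeding is minor.

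On exposure, section 4.4 (Procedures) says "The second, third and fourth phases of the study will last 28 days each". It adds a 21-day first phase on the product that is also used in phase 2.

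On analysis, section 4.6.2 says "The dichotomous outcomes (TTR, thromboembolic events, bleeding) will be analyzed by McNemar's test" and fixes one level throughout ("All statistical analyzes will have a significance level of 5" per cent). Dichotomous outcomes are analysed by intention to treat. Missing data count as unfavourable, and a sensitivity analysis follows.

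The only margin (section 3, 0.49) and the only sample size calculation (section 4.6.1: 48 needed, 60 recruited) concern mean INR. No event rate, margin or precision is given for clinical events, and nothing marks them as descriptive.

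**The concern.** McNemar's test draws its information only from patients who have the event on one product and not on the other. If events are rare over 28 days, there will be almost no such patients, and a non-significant result says nothing about whether the products differ. In a trial framed around equivalence and safe substitution, that result can easily be taken for reassurance.

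The way missing phases are scored adds a second difficulty. The gravest events can end follow-up, and the rule then assigns an unfavourable outcome to products that the patient was not taking when the event occurred.

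**Working it through.** **The plan's own figure.** With a difference of 0.49, SD 0.29, two-sided 5% and 90% power, n per group = 2 × (1.960 + 1.282)² × 0.29² / 0.49² = 7.36, rounded up to 8. Six sequences give 8 × 6 = 48. The stated 48 reproduces, and it is a calculation for INR alone.

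**Inputs for events.** From the protocol: 60 patients (48 as the minimum), 28 days per product in phases 2 to 4, and a 5% level. The two-sided form is stated in section 3 for INR ("two-sided, with a significance level of 5" per cent) and is assumed here for McNemar's test. Event rates are not in the protocol. I assume 1% to 10% per patient-year on the reference product, complete pairs, and independence between phases within a patient.

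**Exposure.**
- Phases 2 to 4: 60 × 28 / 365.25 = 4.60 patient-years per product.
- If phase 1 counts, one product is taken for 21 + 28 = 49 days. The mean is (49 + 28 + 28) / 3 = 35 days, and 60 × 35 / 365.25 = 5.75 patient-years per product.

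**Expected events per product**, as 60 × [1 − exp(−rate × 28/365.25)]: 0.05 at 1% per year, 0.09 at 2%, 0.23 at 5% and 0.46 at 10%. At 2% per year on both products, the chance of no event at all in a pairwise comparison is 83%.

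**What significance requires.**
- Exact test: 5–0 gives 2 × 0.5⁵ = 0.0625 and 6–0 gives 2 × 0.5⁶ = 0.031. At least six discordant patients, all one way, are needed.
- Uncorrected chi-square, (b − c)²/(b + c): 3–0 gives 3.0 and 4–0 gives 4.0, against a critical value of 3.84. At least four, all one way, are needed.

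**Power with 60 pairs**, by enumerating discordant counts:

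| Rates per year | Exact | Uncorrected |
|---|---|---|
| 2% vs 10% | below 0.01% | 0.1% |
| 5% vs 25% | 0.08% | 2.2% |
| 5% vs 50% | 2.0% | 15% |
| 10% vs 30% | 0.16% | 3.1% |
| 10% vs 100% | 20% | 47% |

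Counting phase 1 raises the exact figure for 5% vs 50% from 2.0% to 4.6% (simulation of the six-sequence design). For scale, 80% power to detect a doubling from 5% per year would need about 6,200 pairs.

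**What zero events would show.** With 0 of 60, the one-sided 95% upper limit is 1 − 0.05^(1/60) = 4.9% per 28 days, or −ln(0.05)/4.60 = 0.65 per patient-year. With 48 patients the limits are 6.1% and 0.81.

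**The missing-data rule.**
- A fatal or participation-ending event in phase 2 leaves phases 3 and 4 missing, and both are scored unfavourable. The patient then has an event on all three products, is concordant in every pairwise comparison, and contributes nothing.
- If the event falls in phase 3, the phase 4 product is charged with an event that occurred on another product.
- Unrelated dropout creates imputed discordance. Suppose 20% drop out, with missingness equally likely to begin at phase 2, 3 or 4. For a given pair of products, the chance that a dropout becomes discordant is (1/3)(2/3) + (1/3)(2/3) = 4/9. That gives 60 × 0.20 × 4/9 = 5.3 imputed discordant patients, more than the true event counts above would supply at 5% vs 50% (0.23 + 2.26 = 2.5 events expected).
- Even then, simulated rejection is only 0.8% (2% per year, no difference) to 3.4% (5% vs 50%).

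**Where the point stops.** For bleeding of any grade, at an assumed 10% vs 30% per 28 days, exact power is about 73% with 60 patients and 61% with 48. At 10% vs 20% it is 25% with 60.

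**The case against.** The best defence is that the protocol never claims to settle event risk. Section 2.1 sets the aim as "Determine, through the mean international normalized ratio (INR) of patients, whether there is therapeutic equivalence". Section 3 has a hypothesis for INR only, section 4.5.1 names mean INR as the only primary outcome, and section 4.6.1 sizes the trial on it. The remark on effectiveness and safety sits in a background summary, and no rule turns a non-significant event test into evidence of safety. This stands. A reader might infer that the plan claims power or equivalence for events, or that its sample size is wrong, and the document supports neither reading. What remains is that a 5% test is planned for these outcomes with nothing to limit how its result may be used.

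A reader might also infer that every McNemar test in the quoted sentence is futile. That is not supported. The sentence also covers TTR and bleeding as a whole, minor bleeding included, and power for bleeding of any grade can be reasonable. Section 4.6.2 does not say whether major bleeding is tested separately. Its rate is also uncertain: if the 2.0 g/L criterion captures small falls, major bleeding could be commoner than assumed here.

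Nor can one say that the test fails whatever the truth. The protocol does not specify the exact form, the uncorrected test does better, and at 10% per year with a tenfold difference power reaches 20% to 47%. Phase 1 exposure may count. These points widen the range without making the test useful at 1% to 5% per year.

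Finally, one might say that the pairs needed for McNemar's test would not exist. Under the imputation rule they do exist. The trouble is what they contain, and a sensitivity analysis cannot supply the missing information.

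Details of listings can be left to an SAP. The choice of test and the missing-data rule, however, are fixed in the protocol itself.

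**Conclusion.** The point holds for thromboembolic events, and for major bleeding if it is about as rare. At an assumed 1% to 5% per year, fewer than 0.25 events are expected per product over the 28-day phases. At a 5% reference rate, power is at most 2.2% for a fivefold difference and at most 15% for a tenfold one. A result with no events would be compatible with 0.65 events per patient-year. The missing-data rule makes matters worse, because it can remove the gravest early events from the comparison.

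This rests on assumed rates, complete pairs and independence between phases; it weakens only near 10% per year with a tenfold difference. It limits what these two secondary outcomes can show and leaves the INR comparison untouched. The change is worth making, because the remedy is almost free and prevents an empty p-value from being read as reassurance.

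**What to change.** In section 4.6.2, take thromboembolic events and major bleeding out of the McNemar sentence. For each, report the number of events and the rate per patient-year by the product being taken at onset, with exact confidence intervals, and do not impute missing phases as events. Person-time should then state whether phase 1 is included. TTR and bleeding of any grade are not affected by this change. If major bleeding was never meant to be tested separately, say so and add the descriptive report.

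In section 2.2, label these two outcomes descriptive. Add a sentence that neither a non-significant result nor an absence of events will be taken as evidence of equal thromboembolic or major bleeding risk, and that the conclusion on substitution rests on mean INR, in line with section 2.1.

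The cost is wording and a simpler analysis, with no extra patients or visits. The downside is that these two secondary outcomes have no p-value.
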